### 2.7. Assessment of Feasibility/Safety

Any Adverse Event (AE) will be recorded on the case report form as well as the intercurrent events. Subjects will be examined at each visit or if the subject reports any unusual symptoms. The numbers and severity of such incidents will be included in the statistical analysis. All Adverse events (AEs and SAEs) will be recorded on the AE form. Serious adverse events (SAEs) will be reported to the IRB. Toxicity will be assessed using the National Cancer Institute’s Common Toxicity Criteria for Adverse Events, version 5.0 (CTCAEv5) [32].

A collection of adverse events will be conducted at Visit 2 to individuate the AE rate due to neoadjuvant treatment. Neoadjuvant therapy is usually well tolerated, although some patients can require hospital admission for the management of diarrhea or significant late small bowel toxicity, attributable to radiotherapy [33,34,35,36,37].

A following collection of adverse events will be conducted at Visit 3, before LE, to individuate the AE rate due to added treatment (ECT).

### 2.8. Statistic Considerations

#### 2.8.1. Description of Sample Size Calculation and Planned Statistical Analyses

The sample size was determined by the Group-Sequential Superiority approach with a Margin Tests for the Difference of Two Proportions [36] using a complete response rate to the TRG after local excision as an endpoint. Sample size estimation has been carried out by using the superiority hypothesis in two independent parallel sample proportions [38,39,40,41,42]. According to the literature data, neoadjuvant chemo-radiotherapy treatment in LARC results in a complete response of 25% [43,44,45,46,47,48].

The proportion in the treatment group is assumed to be 0.25 under the null hypothesis and 0.50 under the alternative hypothesis. The proportion in the control group is assumed to be 0.25. The significance level of the one-sided test was targeted at 0.10 and the power at 80%.

An interim analysis will be conducted when 28 patients are enrolled (the percent of the sample size accumulated up to the corresponding look will be 40.0%). If a complete response rate to the TRG after local excision is noted in less than 25% of patients in the treatment group and/or feasibility/safety was not demonstrated, the study will be discontinued, otherwise a further 42 patients will be enrolled in the study.

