#### 2.8.2. Statistical Analysis

The treatment feasibility/safety of surgery following electrochemotherapy will be assessed considering the number of participants with compromised surgery following electrochemotherapy assessed by the R1 resection rate, circumferential resection margin (CRM) involvement, non mesorectal resection plane, and post-operative complications according to the Clavien-Dindo Classification. A surgical complications rate of 30–40% was reported in the literature for conventional neoadjuvant treatment followed by TME [37]. The evaluation of each arm will be performed at Visit 5 (12 weeks from ECT/8 weeks from LE).

Complete response rate (TRG 1 and 2), disease recurrence rates and percentages will be compared among the two groups. A one-sided Fisher exact test will be performed to test the differences between the groups. Differences will be considered significant at *p* < 0.10. A Chi square test will be performed to assess statistically significant differences among the groups for the categorical variable.

The time interval between the recruitment date and local disease progression will be represented using the time of treatment failure and median and minimum–maximum values will be considered.

The scores obtained by the QOL, pain and satisfaction questionnaires will be evaluated. Any serious adverse events and their intensity, according to the NCI-CTCAE classification (version 5.0), will be registered in the first two days post-procedure.

Mean ± standard deviation will be considered for normally distributed continuous variables while the median and interquartile range (IQR) will be presented for non-normally distributed continuous variables.

For continuous variables, the difference between follow-up values and baseline values will be tested by a 2-sided Student t-test or by a Mann–Whitney test while, for the categorical variables, the McNemar test and the marginal homogeneity test will be use [49,50].

Time to event outcomes will be analyzed using the Kaplan–Meier method and survival curves will be compared using the log-rank test.

Mixed effect regression models will be used to analyze longitudinal data by adjusting for proper covariates.

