#### 2.8.3. Interim Analysis

Interim analyses will be fixed after the first step of the study. A conclusive analysis will be performed at the end of the treatment of patients enrolled in the second stage. If a complete response rate to the TRG after local excision is noted in less than 25% of patients in the treatment group, and/or feasibility/safety was not demonstrated, the study will be discontinued. A difference of 20% for both AE rate and surgical complications rate between the two arms will be considered significant enough to discontinue the trial.

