## 3. Discussion

The efficiency and safety of ECT have been demonstrated in preclinical and clinical Phase I and I/II studies in patients with melanoma, head and neck squamous cell carcinoma, Merkel cell carcinomas, basal cell carcinoma and adenocarcinoma nodules. The efficacy of ECT has already been proven in skin tumors, and in mucosal and submucosal tissues with high tumor control. Recent studies have demonstrated the feasibility and safety of ECT in the treatment of deep tumors (locally advanced pancreatic cancer, hepatic colorectal metastases, cancerous thrombosis of the portal vein, cholangiocarcinoma hepatocellular carcinoma) [10,11,12,13,14,15,16,17,18,19,20,21,22,23,24,25,26]. In addition, ECT has been used as a neoadjuvant treatment for tumor downstaging before surgical treatment to increase the rate of conservative surgical interventions.

Moreover, colorectal cancer as well as gastric and esophageal tumors have been treated with endoluminal electrodes without adverse events or complications demonstrating a tumor regression (https://clinicaltrials.gov/ct2/show/NCT03040180, accessed on 10 April 2021) [27].

Currently, 45–55% of rectal cancer patients receive preoperative chemo-radiotherapy for LARC. TME is the gold standard in rectal cancer surgery and is comprised of resection of the rectum together with the fatty tissue surrounding the rectum [45]. For LARC, therapy consists of preoperative chemo-radiation therapy (pCRT) or radiotherapy alone followed by TME [51,52,53,54,55,56,57,58,59,60,61,62].

The high morbidity and functional complications associated with TME motivate the search for conservative treatments with sphincter preservation for patients with early rectal cancer at diagnosis and patients with significant tumor regression after pCRT, with the advantage of reducing morbidity and providing a “true” organ-sparing approach [42]. It has also been suggested that a prolongation of the treatment interval might improve overall survival [63,64,65].

Complete pathological response after neoadjuvant therapy in rectal cancer has been shown to be an independent predictor of overall survival and a decrease in local recurrences; up to 30% of patients will achieve a complete or near complete response [46,47,48].

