## Figures and Tables

**Figure 1 cancers-13-03199-f001:**
[figure not shown]
Trial design flowchart.

**Table 1 cancers-13-03199-t001:** Inclusion and Exclusion Criteria.

Inclusion Criteria	Exclusion Criteria
Patients of both sex aged ≥18 years	Age less than 18 years
Histological confirmation of rectal adenocarcinoma	Patients with neoplasia more than 12 cm from the anal margin
Patients undergoing neoadjuvant treatment for locally advanced tumor of the rectum with confirmed major clinical response after neoadjuvant treatment	Patients with stable disease or disease progression after neoadjuvant treatment
Rectal tumor up to 12 cm from the external anal margin	Patients who, for medical reasons, cannot be given bleomycin
Patients must be willing to comply with the study protocol and give their informed written consent	Lesions unsuitable for Electrochemotherapy (ECT) (bony invasion, large vessels infiltration, etc.)
Patients with an Eastern Cooperative Oncology Group (ECOG) status performance <3	Acute lung infection
	Poor lung function symptoms
	Severe coagulation disorders
	Previous allergic reactions to bleomycin
	Previous cumulative bleomycin dose over than 250 mg/m^2^
	Chronic renal dysfunction (creatinine> 150 µmol/L)
	Pregnancy or lactation

**Table 2 cancers-13-03199-t002:** Visits Scheme.

Visit #		1	2	3	4	5	6	7	8	9
**Time**		Month −1 (up to 1 month prior the treatment)	Day 0 ± 3 days	Day 30 ± 3 days	Day 37 ± 3 days	12 ± 1 week	24 weeks ± 1 week	36 ± 1 week	48 ± 1 week	60± 1 week
	**Visit Description**	Restaging, enrolment, randomization	Treatment group: Electrochemotherapy	Local Excision	Histological examination	Follow up visit	Follow up visit	Follow up visit	Follow up visit	Follow up visit

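### The 25% used as control rate, null rate and interim cut-off is not a rate for this trial's population or endpoint, so the response part of the futility look weakens as the true rate rises above 25%

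*Protocol article*

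**What the plan says.** Section 2.8.1 of the protocol article takes its planning rate from the literature: "neoadjuvant chemo-radiotherapy treatment in LARC results in a complete response of 25" per cent. From this it sets the design: "The proportion in the control group is assumed to be 0.25", and "The proportion in the treatment group is assumed to be 0.25 under the null hypothesis and 0.50 under the alternative hypothesis". The same 25% returns as the interim cut-off in Sections 2.8.1 and 2.8.3. After 28 patients the trial is to be discontinued if response is "noted in less than 25% of patients in the treatment group", or if feasibility/safety is not shown.

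The patients are described differently. Table 1 admits "Patients undergoing neoadjuvant treatment for locally advanced tumor of the rectum with confirmed major clinical response after neoadjuvant treatment" and excludes stable or progressive disease. Sections 2.3.1 and 2.3.2 repeat the restriction. Section 2.5.1 defines major clinical response by the absence of a palpable mass, of pathological nodes on MRI and of ulcers larger than 2 cm.

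The endpoint is also described differently. Section 2.6 counts TRG 1 and 2 as response, and Section 2.8.2 states "Complete response rate (TRG 1 and 2), disease recurrence rates and percentages will be compared among the two groups". The Discussion gives a separate figure for the wider category, again without restriction to clinical responders: "up to 30% of patients will achieve a complete or near complete response".

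The Abstract and Section 2 describe the go decision in other terms. There the second stage follows if a rise in response is seen, and/or if feasibility/safety is shown.

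**The concern.** A rate quoted for complete response in LARC is applied to a group already selected for good clinical regression, and to an endpoint that adds TRG 2. Selection on a marker of regression should raise the regression rate, and so should a wider definition of response. The document adjusts for neither.

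A randomised final comparison can absorb a wrong control rate, but a fixed cut-off in one arm cannot. If patients without ECT already respond more often than 25%, an ECT that adds nothing will tend to clear the cut-off, and up to 42 more patients will be enrolled. The 14 concurrent controls, who would show whether 25% is right, play no part in the response rule. The hypotheses also lose their meaning: if controls respond at 50%, a 50% rate under ECT is no effect.

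**Working it through.** **The plan's own figure.** Inputs from Sections 2, 2.2 and 2.8.1: 25% vs 50%, one-sided alpha 0.10, 1:1 allocation, 70 patients (35 per arm). By the normal approximation with pooled variance under the null:

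- mean rate 0.375; null SE = √(2 × 0.375 × 0.625 / 35) = 0.1157
- alternative SE = √((0.25 × 0.75 + 0.50 × 0.50) / 35) = 0.1118
- power = Φ((0.25 − 1.2816 × 0.1157) / 0.1118) = Φ(0.91) = 0.818

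The fixed design needs 33 per arm. Two-look designs at 40% information need 34 to 38 per arm with the same pooled variance, depending on the spending function. The stated 35 per arm is therefore consistent with its inputs.

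**The interim rule.** Stage 1 has 14 patients in the ECT arm. Since 25% of 14 is 3.5, a rate under 25% means 3 or fewer responders. The chance of stopping is the exact binomial P(X ≤ 3), n = 14, at true ECT-arm rate p. For p = 0.25 the terms for 0, 1, 2 and 3 responders are 0.018, 0.083, 0.180 and 0.240, which sum to 0.521. If ECT adds nothing, p equals the control rate:

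| True rate with no ECT effect | Present rule stops | Comparative rule stops |
|---|---|---|
| 25% | 52% | 41% |
| 30% | 36% | 42% |
| 35% | 22% | 42% |
| 40% | 12% | 42% |
| 50% | 2.9% | 43% |
| 60% | 0.4% | 42% |
| 70% | <0.1% | 42% |

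The comparative rule stops if ECT responders are fewer than control responders among the first 14+14. Its figures come from exact enumeration of two independent binomials.

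**How far above 25%?**

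- Wider endpoint alone: by the Discussion's figure, complete or near complete response is at most 30%. The chance of stopping then falls from 52% to 36%.
- Selection: the documents give no figure. As an assumption, let a share f of LARC patients be major clinical responders, and let all pathological responders be among them. The rate in the trial is then the base rate divided by f.
  - From 25%: f = 0.8, 0.6, 0.5 gives 31%, 42%, 50%, and the rule stops 32%, 10%, 2.9%.
  - From 30%: the same shares give 37.5%, 50%, 60%, and the rule stops 17%, 2.9%, 0.4%.

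**Final test.** This is the exact power of the one-sided Fisher test at p < 0.10, 35 per arm, for a 25-point gain and no interim stop: 73.8% at 25 vs 50%, 71.4% at 40 vs 65%, 73.8% at 50 vs 75%, 81.3% at 60 vs 85%. With equal rates, the type I error stays between 5.9% and 6.6% at the control rates computed from 25% to 80%.

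**Cost of the comparative rule** (exact enumeration, 14+21 per arm):

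| Control vs ECT | Wrong stop, present | Wrong stop, comparative | Power, present | Power, comparative |
|---|---|---|---|---|
| 25% vs 50% | 2.9% | 5.5% | 72.8% | 72.7% |
| 40% vs 65% | 0.1% | 6.1% | 71.4% | 70.3% |
| 60% vs 85% | <0.1% | 3.9% | 81.3% | 80.3% |

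**The case against.** The strongest reply is that the size of the problem is unknown. No passage gives a TRG 1-2 rate among major clinical responders. The wider endpoint by itself moves the rate to 30% at most, and the rest depends on a responder share that the documents do not state. The sources behind the 25% are not at hand, and some are also cited for the 30% figure, so the 25% may already include some near-complete responses. A reader might infer that the 25% rule can hardly ever fire. That needs a true rate of roughly 45-50% or more, and the documents do not support it: at 30-40% the rule still stops 12-36% of the time. This part of the reply stands and limits the point.

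A reader might also infer that the trial has lost its power, or that an ineffective ECT could now be declared effective. Neither follows. Section 2.8.1 plans for a difference in proportions, and power for 25 points is much the same at higher control rates. A loss appears only if the effect is held constant as an odds ratio, which the protocol does not do. The final Fisher test compares randomised concurrent arms and keeps its error rate at any control rate.

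The interim also has a second limb. Section 2.8.3 allows discontinuation for a between-arm difference in adverse events and surgical complications, and this point does not touch it.

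Finally, counting TRG 1-2 fits the organ-sparing aim, since Section 2.6 makes TRG above 2 a ground for TME. Restricting the endpoint to TRG 1 would be a trade-off, so it is not asked for here.

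The reply leaves the mismatch itself unanswered. Both differences push the same way, the document adjusts for neither, and a single-arm cut-off is sensitive to exactly this figure.

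**Conclusion.** The point holds in a limited form. The 25% is stated for complete response in LARC, yet it serves as control rate, null rate and stopping threshold in a trial of major clinical responders with TRG 1-2 as the endpoint. The expected no-effect rate lies above 25% by an undocumented amount. The response part of the futility look does its intended work only near 25%: it stops an ineffective ECT 52% of the time there, 36% at 30%, 12% at 40% and 2.9% at 50%. The direction rests on the text. Where the trial falls on that scale rests on the unstated responder share.

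The damage is a weak futility look, costing up to 42 further patients, and a null and target of 25% and 50% that may not describe this population. The validity of the final comparison, the power for a 25-point gain and the safety limb are not affected.

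**What to change.** 1. In Section 2.8.1, justify or restate the control rate for TRG 1-2 in patients with major clinical response. Show power at 35 per arm over a range of control rates such as 25-70%, using the planned Fisher test.

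2. In Sections 2.8.1 and 2.8.3, replace the fixed single-arm 25% by a comparison with the concurrent controls. For example, stop for futility if ECT responders are fewer than control responders among the first 14+14. State the rule's operating characteristics, and say that ties continue. Align the Abstract and Section 2, which already speak of a rise in response, and reconcile their and/or wording with the stopping text.

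Cost: changes of wording and no extra patients for the interim rule. At 25% vs 50%, wrong stopping rises from 2.9% to 5.5%, and Fisher power is 72.7%, against 72.8% under the present rule and 73.8% with no interim stop. At higher control rates power falls by about one point. If the true no-effect rate really is 25%, the comparative rule stops somewhat fewer ineffective trials than the present one (41% against 52%). In return, the stopping rate stays at 41-43% for control rates from 25% to 70%. If restating the control rate leads to a target gain smaller than 25 points, the sample size would have to be derived again.

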#### 2.8.2. Statistical Analysis

The treatment feasibility/safety of surgery following electrochemotherapy will be assessed considering the number of participants with compromised surgery following electrochemotherapy assessed by the R1 resection rate, circumferential resection margin (CRM) involvement, non mesorectal resection plane, and post-operative complications according to the Clavien-Dindo Classification. A surgical complications rate of 30–40% was reported in the literature for conventional neoadjuvant treatment followed by TME [37]. The evaluation of each arm will be performed at Visit 5 (12 weeks from ECT/8 weeks from LE).

Complete response rate (TRG 1 and 2), disease recurrence rates and percentages will be compared among the two groups. A one-sided Fisher exact test will be performed to test the differences between the groups. Differences will be considered significant at *p* < 0.10. A Chi square test will be performed to assess statistically significant differences among the groups for the categorical variable.

The time interval between the recruitment date and local disease progression will be represented using the time of treatment failure and median and minimum–maximum values will be considered.

The scores obtained by the QOL, pain and satisfaction questionnaires will be evaluated. Any serious adverse events and their intensity, according to the NCI-CTCAE classification (version 5.0), will be registered in the first two days post-procedure.

Mean ± standard deviation will be considered for normally distributed continuous variables while the median and interquartile range (IQR) will be presented for non-normally distributed continuous variables.

For continuous variables, the difference between follow-up values and baseline values will be tested by a 2-sided Student t-test or by a Mann–Whitney test while, for the categorical variables, the McNemar test and the marginal homogeneity test will be use [49,50].

Time to event outcomes will be analyzed using the Kaplan–Meier method and survival curves will be compared using the log-rank test.

Mixed effect regression models will be used to analyze longitudinal data by adjusting for proper covariates.

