#### 2.3.1. Control Group Treatment

Patients undergoing neoadjuvant treatment for LARC with a major clinical response at restaging will undergo a local excision 16 (±1) weeks after the end of neoadjuvant therapy and histopathological examination with TRG evaluation. Local excision can be performed either with the conventional technique (TAE), or the Transanal endoscopic microsurgery (TEM) or other techniques (TAMIS), provided that the following principles are respected: free macroscopic margin of at least 0.5 cm, full thickness excision, fixation of the operative piece on support to facilitate the histological interpretation of the pathologist.

After histopathological examination, based on pathological findings, Total Mesorectal Excision (TME) can then be planned for the patients if, as expected from clinical practice, ypT ≥ 2, there is the presence of positive margins, TRG > 2 and the cancer is poorly differentiated (G3).

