#### 2.3.2. Experimental Group Treatment

In the treatment arm, patients undergoing neoadjuvant treatment for LARC with major clinical response at restaging will undergo Electrochemotherapy (ECT) 12 (±1) weeks after the end of neoadjuvant therapy. After four weeks (±5 days) of ECT, the patients will undergo a surgical treatment with local excision and histopathological examination with TRG evaluation.

After histopathological examination, based on pathological findings, TME can be planned for the patients.

Patients will receive Bleomycin intravenously (15,000 IU BLM/m^2^) and after 8 min, an electric pulse delivered to the lesion will be performed with the CLINIPORATOR™ (IGEA Ltd., Modena, Italy) with the insertion of appropriate CE certificate electrodes for endoluminal treatment [4]. The procedure must be completed within 40 min from the end of the bleomycin injection. The anesthesia will be induced after bleomycin injection and before the application of the electrodes in the case of local anesthesia, or before bleomycin injection in the case of general anesthesia.

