The major clinical response after neoadjuvant treatment will be evaluated 12 weeks from the end of radiotherapy with the following tests: laboratory exams, CEA dosage, CT of chest and abdomen with contrast medium, MR pelvis with contrast medium and rigid rectoscopy. The major clinical response is classified as the absence of palpable mass to the digital exploration of the rectum and pathological lymph nodes (>5 mm of diameter along the short axis) to the pelvic MRI, and the absence of deep or superficial ulcers > 2 cm of diameter, at rectoscopy.

#### 2.5.2. Visit 2

The patients with confirmed eligibility will be treated with ECT. The type of anesthesia will be determined by the anesthesiologist. The patients will undergo clinical evaluation, pain assessment by VAS score and blood samples and CEA dosage. The use of concomitant treatment or drug for pain control will be registered.

#### 2.5.3. Visit 3

At day 30 ± 3 (Visit 3), all patients randomized in the control or treatment group will be subjected to LE according to established clinical and institutional practices. The patients will undergo the same procedures as above and according to timing reported in Table 2: Evaluation of routine hematochemistry and CEA, pain assessment by VAS scale and Quality of Life (life quality evaluation according to EQ5d questionnaire) will be completed.

#### 2.5.4. Visit 4

The patients will undergo histological examination; surgical specimens containing the tumor will be evaluated and scored according to TRG, as proposed by Mandard et al. [28], by an expert pathologist who is not aware of the clinical and diagnostic findings. Adverse events/complication will be recorded. Pain evaluation and QoL will be assessed.

#### 2.5.5. Visit 5, 7, 9, 11

After clinical evaluation, the patients will be submitted to rectoscopy, colonoscopy, pain assessment by VAS score and blood samples and CEA dosage. The use of concomitant treatment or drugs for pain control will be recorded. Adverse events/complication will be noted.

#### 2.5.6. Visit 6, 10, 13, 15, 17

After clinical evaluation, the patients will be submitted to rectoscopy, colonoscopy, MRI, pain assessment, blood samples and CEA dosage as above. The use of concomitant treatment or drugs for pain control will be recorded. Adverse events/complication will be noted.

#### 2.5.7. Visit 8, 12, 14, 16, 18

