After clinical evaluation, the patients will be submitted to rectoscopy, colonoscopy, CT, MRI, clinical evaluation, pain assessment, blood samples and CEA dosage as above. The use of concomitant treatment or drugs for pain control will be recorded. Adverse events/complication will be noted.

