### 2.6. Assessment of Efficacy

The response of treatment in both the control arm and the treatment arm will be assessed with the histopathological TRG on tissue specimens after local excision.

The total number of cases with TRG 1 and 2 [28] will be recorded and the proportion of responses will be compared between the two groups.

If the histological examination documents the presence of carcinoma with at least one of the following characteristics: 1. ypT ≥ 2; 2. Positive margins; 3. TRG > 2; 4. Poorly differentiated form (G3), the local excision will be considered inadequate treatment and the patient will undergo TME.

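### Surgical safety is read at Visit 5, timed from ECT and local excision, so outcomes of a TME that follows later may be incomplete in the comparison and in the 20% stopping rule

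*Protocol article*

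**What the plan says.** Feasibility/safety is the first primary endpoint (Section 2.1.1). Section 2.8.2 measures it by "R1 resection rate, circumferential resection margin (CRM) involvement, non mesorectal resection plane, and post-operative complications according to the Clavien-Dindo Classification" and gives this benchmark: "A surgical complications rate of 30–40% was reported in the literature for conventional neoadjuvant treatment followed by TME". It then sets the time: "The evaluation of each arm will be performed at Visit 5 (12 weeks from ECT/8 weeks from LE").

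The operation that every patient has is local excision (LE): "At day 30 ± 3 (Visit 3), all patients randomized in the control or treatment group will be subjected to LE" (Section 2.5). Table 2 puts the histology at Visit 4, Day 37 ± 3, and Visit 5 at 12 ± 1 weeks. TME comes only after that histology. Section 2.6 says that if any one of four adverse features is found, "the local excision will be considered inadequate treatment and the patient will undergo TME". Section 2.3.1 says of controls that "Total Mesorectal Excision (TME) can then be planned for the patients", and joins its criteria with *and*. Section 2.3.2 says of the ECT arm: "After histopathological examination, based on pathological findings, TME can be planned for the patients", without listing criteria. No section dates TME, and Table 2 has no TME visit and no second histology.

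The surgical complication rate also feeds Section 2.8.3, where a 20% difference between the arms is a ground for stopping the trial. After Visit 5, events are still collected: "Adverse events/complication will be noted" (Section 2.5, later visits).

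**The concern.** CRM involvement and the mesorectal plane describe a TME specimen, and the 30–40% benchmark is a TME rate. Yet the clock for the evaluation runs from ECT and LE. A patient sent to TME after the LE histology brings whatever TME follow-up happens to have accrued by Visit 5. That may be a full post-operative period, part of one, or none.

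The number sent to TME depends on response, which is what the treatment is meant to change. If the arms differ in response, they differ in how many patients are open to incomplete counting. A primary endpoint and a stopping rule would then rest on a count whose completeness depends on an unstated date and may differ by arm.

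**Working it through.** **Inputs.** LE Day 30 ± 3, histology Day 37 ± 3, Visit 5 at 12 ± 1 weeks (Day 84, range 77 to 91), Visit 6 at 24 ± 1 weeks (Day 168, range 161 to 175), all from Table 2. Response (TRG 1–2) 25% in control and 50% with ECT under the alternative; 70 patients, 1:1, interim at 28 (Sections 2, 2.2, 2.8.1). TME complications 30–40% (Section 2.8.2). Assumption: a 30-day post-operative period.

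**1. The plan's own figures.**
- LE to Visit 5: 84 − 30 = 54 days = 7.7 weeks, which agrees with the stated 8 weeks.
- The response rates are those behind the sample size. For 0.25 versus 0.50, one-sided 0.10 and 80% power, a fixed design needs 33 per arm; 35 per arm gives 81.8% power.

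**2. Time available for TME before Visit 5.**
- Histology to Visit 5: 84 − 37 = 47 days. With windows: 77 − 40 = 37 to 91 − 34 = 57 days.
- Latest TME that leaves 30 days: 47 − 30 = 17 days after histology (7 to 27 with windows).
- TME at 4, 6 or 8 weeks after histology (assumed range) falls on Day 65, 79 or 93 and leaves 19, 5 or 0 days.

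**3. Patients exposed**, counting TRG > 2 alone under Section 2.6.

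| | Control | ECT |
|---|---|---|
| Final, 35 per arm | 0.75 × 35 = 26.25 | 0.50 × 35 = 17.5 |
| Interim, 14 per arm | 0.75 × 14 = 10.5 | 0.50 × 14 = 7 |

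Under the null (25% in both arms) the expected numbers are equal. The other features in Section 2.6 could add patients. The permissive wording of Sections 2.3.1 and 2.3.2, and better response in patients already selected as major responders, could reduce them.

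**4. What can be hidden if ECT spares TME.** Share with a TME complication, per randomised patient:
- Control: 0.75 × (0.30 to 0.40) = 22.5% to 30%.
- ECT: 0.50 × (0.30 to 0.40) = 15% to 20%.
- Difference: 7.5 to 10 points in favour of ECT with full capture, 0 with none.

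**5. Effect on the 20-point rule at 14 per arm**, read as ECT exceeding control by at least 20 points. Assumptions: LE complications 10% in both arms and independent of TME complications; a fraction f of TME complications is captured. The arm rate is 1 − (1 − 0.10)(1 − TME share × TME complication rate × f), with binomial counts.

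| Captured, f | Same TME rate (35% both): control / ECT rate, chance of 20 points | Worse TME after ECT (35% vs 70%): control / ECT rate, chance of 20 points |
|---|---|---|
| 1 | 33.6% / 25.8%, 7% | 33.6% / 41.5%, 29% |
| 0.5 | 21.8% / 17.9%, 7% | 21.8% / 25.8%, 19% |
| 0 | 10% / 10%, 5% | 10% / 10%, 5% |

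With LE rates of 5% to 20% in the second scenario, the chance is 28–30% with full capture and 2–12% with none. If ECT only spares TME, truncation barely moves the stopping rule; what is lost is the 7.5 to 10 points. If ECT makes later TME harder, the rule loses most of its ability to respond.

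**The case against.** The strongest reply is that the loss depends on a date that the article does not give. A TME within 17 days of histology would have its 30 days, its margins and its plane by Visit 5. A condensed article may also leave the scheduling of a second operation to the full protocol. This stands. A reader might infer that the Visit 5 reading cannot capture TME outcomes, but the documents support only that it may not capture all of them.

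A reader might also infer that surgical safety closes at Visit 5 and that later harm goes unseen. The text does not say so. Section 2.4 records any event during treatment and follow-up, Section 2.5 notes complications at the later visits, and Section 2.7 brings the number and severity of events into the analysis. Late TME complications are therefore recorded. What remains is narrower: Section 2.8.2 does not bring them into the surgical-safety evaluation.

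Third, if the operation meant is LE, about 54 days are observed in both arms and nothing is cut off. But CRM, the mesorectal plane and the TME benchmark do not fit LE, so that reading leaves the measures without a matching operation.

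Finally, an early fixed reading has a proper use in a safety rule, and moving everything to week 24 would delay a stop by up to 12 weeks. This stands and limits the fix.

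**Conclusion.** The point holds as a risk of an incomplete comparison, not as a certain loss. The evaluation time is stated, is tied to ECT and LE, and applies to measures that belong largely to a later operation. For a 30-day period (assumed), only a TME within about 17 days of histology (7 to 27) is fully counted.

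At the planning rates, and if TRG > 2 leads to TME as Section 2.6 says, about 26 of 35 control and 17 to 18 of 35 ECT patients are exposed. The TME-driven difference at stake is 7.5 to 10 points in favour of ECT, taking the plan's 30–40% rate as valid for a TME after LE. A harm of ECT to later TME can equally be hidden; the size shown for that case rests on illustrative rates that are not in the documents.

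A reader might infer that one arm is always disadvantaged. The documents do not support this: with equal response rates the expected exposure is equal, and with unequal rates the direction depends on whether ECT spares TME or makes it harder.

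**What to change.** In Section 2.8.2:
- Count surgical complications over the same fixed period (for example 30 days) from the date of each operation: LE and, where done, TME.
- Take R1, CRM and plane from the TME specimen whenever TME is done.
- Report LE and TME outcomes separately by arm, with all randomised patients as denominator, because patients who reach TME are selected by response after randomisation.
- Complete the final endpoint for TME patients from visits already scheduled. Visit 6 (Day 168) holds a 30-day period for TME up to 168 − 30 − 37 = 101 days after histology (91 to 111 with windows).
- Keep the Visit 5 reading for LE and for the interim safety rule. Add all TME outcomes available by then, and state how many TME patients have incomplete follow-up. A 30-day LE period ends by Day 63 at the latest (33 + 30), before the earliest Visit 5 on Day 77.

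Sections 2.3.1, 2.3.2 and 2.6 must be reconciled on when TME follows, since the number of patients concerned depends on it.

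The cost is protocol wording, an operation-date field and a somewhat later final surgical-safety reading for TME patients. No visit or procedure is added, and the interim safety reading is not delayed.
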